### The current trial

Providing TIC in residential treatment services for young people may help ameliorate problematic substance use and reduce risk of relapse (25) as well as improve symptoms of PTSD (20). The current trial aims to: (i) determine the feasibility of implementing a new model of TIC in a youth (18–35 years) residential substance use treatment service, (ii) evaluate the impact on client, staff, and service outcomes, and (iii) examine the sustainability of the delivery of the TIC model once the formal evaluation ends.

The frameworks used to guide the current project were the “Consolidated Framework for Implementation Research” (CFIR; (57)) and the “Exploration, Preparation, Implementation, Sustainment” [EPIS; (58)] framework. CFIR offers a comprehensive approach to understanding the dynamic factors influencing intervention implementation across individual, team, and organizational levels. This allowed us to systematically assess key constructs, such as intervention characteristics, inner and outer settings, individual characteristics, and implementation process, to inform our implementation strategies. The EPIS framework was used to develop a structured phased approach that provided sequential phases of exploration, preparation, implementation, and sustainment. This combined approach enabled us to better understand the organizational context, stakeholder engagement, and potential barriers and facilitators throughout each planned phase, and provided a structure to develop an intervention with longevity post research involvement.

## Methods and analysis

### Trial design and sample selection

This single-armed, uncontrolled Phase 1 implementation trial will develop and implement a new model of TIC into one residential treatment service in Queensland, Australia and evaluate client, staff, and service outcomes. The service currently provides a live-in six-week treatment program for young people aged 18–35 years with substance use problems, using individual and group-based therapy.

The sample for the study will be clients and staff in the participating residential treatment service, who consent to participate in the TIC evaluation. Staff include counselors/case managers; management; medical staff such as nurses and psychiatry registrars; night and support staff. Non-identifiable service data will also be collected. The Standard Protocol Items for Randomized Trials (SPIRIT) checklist was adhered to during the development of this protocol, see Appendix 1.

#### Patient and public involvement

To assess the specific needs of the residential service, qualitative interviews were conducted with 20 residential staff and 18 clients (59). The development of the research question and outcome measures was informed by this qualitative research. Both staff and clients perceived comorbid SUD and PTSD to be a significant challenge in residential treatment and recognized the need for integrating TIC and PTSD treatment in these settings. However, staff had an inconsistent understanding of what it means for a service to become trauma-informed and reported considerable variability in their practical skills for managing trauma (59). The model was co-designed with residential service clients, staff, and management, based on existing models of TIC that were developed for adult outpatient services (60). Codesign occurred between February and July 2020. After the qualitative interviews and initial consultations, the model was refined in collaboration with residential service clients, staff, and management. There was no patient involvement in the recruitment to and conduct of the study. The trial results will be disseminated in the form of a report to the treatment services.

### The trauma informed care model

The core components of the new TIC model of care, described below, include: workforce development, adapting the program and broader service environment, screening for trauma, and providing trauma-focused therapy. A Logic Model provides an overview of the development and proposed implementation and outcomes of the TIC model of care (see Figure 1).

**Figure 1 fig1:**
[figure not shown]
Logic model for the newly developed trauma-informed model of care in residential youth treatment for substance use disorders.

#### Workforce development

Following recommendations from research and practice for how to implement TIC models for SUDs (21, 28, 61), workforce development had the following aims: ensure staff working with clients have an awareness of the extent of trauma exposure, increase understanding of the consequences of trauma exposure and its impact on behavior and recovery, facilitate recognition of the signs and symptoms of trauma-related disorders, and develop skills to apply this knowledge in practice using brief intervention strategies (61). A 2-day training workshop for staff was developed and delivered by a clinical psychologist with specialist skills in TIC in August 2020. The aim of the workshop was to build staff knowledge of TIC, and their skills and confidence in trauma screening, feedback, and management of trauma-related behaviors in residential AOD treatment settings. A summary of the workshop content is provided in Table 1.

**Table 1 tab1:** Essential areas of trauma-informed care included in the staff training.

Topic	Details
*Introductory skills in trauma-informed care*	
Defining trauma	Defining trauma in line with the DSM-5 definitions, and presenting the differences between single event and complex trauma. Discussing the neuroscience and physiological consequences of trauma. Research around trauma and substance use (e.g., Adverse Childhood Experiences research), and the effects of trauma on health.
Secondary and vicarious trauma	Recognizing vicarious and secondary trauma in AOD staff.
Introduction to trauma-informed care	Covering the five principles of trauma-informed care. Discuss how TIC is beneficial for both staff and clients. Considerations of TIC for different minority and vulnerable groups (e.g., culturally and linguistically diverse peoples), with reference to intergenerational trauma.
*Advanced residential-specific skills*	
Unpacking complex trauma	Discussion of factors than affect recovery such as developmental stage, support, stress, pre-morbid functioning, and type of trauma. The role of disrupted attachment and early interpersonal trauma that will be prevalent in AOD residential clients.
The consequences of complex trauma	Discussing the consequences of trauma on emotions and cognitions, and how this can present following single incident versus complex trauma, including: emotion dysregulation, maladaptive coping styles, negative beliefs about self, disconnection from the body, interpersonal difficulties.
Understanding challenging behaviors	Teaching staff to identify potentially challenging behaviors in clients and understand why they may be present in specific contexts.
Symptoms that can present as a result of trauma	Training to identify potential symptoms of trauma history and facilitate understanding of the function of these for clients, including: suicidality and self-harm (thought/plan/intent to deliberately self-harm or die by suicide), psychosis (hallucinations, delusions, grossly disorganized behavior), dissociation (transient periods of cognitive-perceptual disturbance in response to stress).
Managing and presenting vicarious trauma	Symptoms of vicarious trauma, and how these may arise in certain work contexts or to certain people (i.e., vulnerability factors). Facilitating staff to identify vicarious trauma through five recurring factors. Organizational strategies to prevent or alleviate vicarious trauma. Tips for practice and screening tools for staff.
PTSD screening in clients	Staff understanding of the importance of screening for PTSD in clients, and how to administer and interpret this.
Conversations on trauma	Teaching staff skills on talking about trauma with clients and how to contain disclosures of trauma.
Managing triggers and distress	Teaching staff how triggers for clients can lead to emotion dysregulation and how to deal with this, including: how to respond in the moment, creating a sense of safety for clients, grounding exercises.
Responding to trauma symptoms	Teaching staff on how to respond to: suicidal ideation, triggers, psychotic experiences, dissociation, aggression, challenging behaviors, conflicts between clients.
Importance of formulations	Using formulations for clients to help inform treatment, particularly when challenging behavior arises.
What TIC looks like in practice	Looking at what the organization is currently doing that is trauma-informed, and what changes need to be made to make it more trauma-informed, and discussing potential barriers to this. How AOD services can inadvertently retraumatise clients and how to minimise this.

Clinical supervision in the new TIC model following the workshop will be provided to staff involved in direct client care, to help consolidate their knowledge, skills, and confidence in TIC. The process of supervision will involve support in the new model and critical reflection through the lens of TIC principles. Weekly supervision will involve a 1:2 ratio of supervisor to supervise for 40 min each week. This will be provided by a clinical psychologist and member of the project team during the initial implementation of the TIC model. Once the formal evaluation has finished, period, supervision will be provided by a team leader/ manager within the service who has received training from a clinical psychologist in TIC supervision practices.

#### The service environment

The procedures, practices, and physical setting of the residential facility were reviewed by the research team and staff to target the key TIC principles of safety, trust, choice, collaboration, and empowerment in the service environment. The staff, assisted by the researchers and TIC specialized clinical psychologist developed a poster that highlighted TIC practices at the residential service. Key changes that were made after this review included a staff member allocated to a floor manager position, responsible for monitoring and managing client behavior and the day-to-day activities of the service, including adherence to the program schedule.

Staff will be provided with trauma-informed guidelines to reinforce the training content. The guidelines include examples of how to discuss trauma with clients, preparing for and managing trauma disclosures, strategies for creating a safe environment (e.g., speaking in soft and gentle tone, attending to non-verbal’s, being aware of body and positioning, normalization, and validation practices), and example scripts and strategies for managing and preventing distressing trauma-related responses in clients. Additionally, staff will be provided with information on taking a strength-based approach (rather than a deficit model), supplemented with resources for staff and clients, and posters on site.

#### The group treatment program

The existing 6-week therapeutic group program was extensively revised by the research team with staff to create a more structured, consistent, and trauma-informed approach, described below. Three one-day training workshops on the new program were delivered by the research team to residential staff across 2020 and 2021. Staff were encouraged to provide feedback on the program throughout training to further refine the content. Staff who are in the role of treatment facilitators will deliver the 6-week therapeutic program.

Clients entering the service will take part in a 1 h introductory group, developed to: (i) provide clients with a general overview and feedback on their routine Outcome Measures collected at treatment entry; (ii) enhance clients’ motivation to complete residential treatment using a motivational interviewing framework (e.g., completing decisional balance form on staying versus leaving residential facility); and (iii) understanding the benefits and skills they will practice during the residential program.

Clients will take part in ‘Grit’, an 12-session strength-based, self-regulation and wellbeing program (62); ‘Healthy Recovery’, a 6-session intervention targeting health behaviors for people in treatment for SUDs (63); and ‘ReFrame’, a 12-session Cognitive-Behavior-Therapy (CBT) intervention for substance use. The content of each intervention is summarized in the Supplementary Tables S1–S3. Additional group sessions may also be conducted outside of this program, which clients can attend if the content is relevant to their needs and goals (e.g., parenting group, gambling group, Alcoholics Anonymous).

##### Trauma-informed components

Psychoeducation on the impacts of trauma and links with SUDs was integrated into the three group interventions. Specifically, Grit was adapted to include sessions exploring of the impacts of long-term stress (including trauma) on the body, how early stress and adverse childhood experiences can impact relationships and schemas of the world, and coping skills designed for managing strong emotions arising from stress. The link between trauma and adverse childhood experiences and substance use was also embedded into the program content. The content of the program was also evaluated to ensure its consistency with TIC, through ensuring that: (i) there were no aggressively confrontational practices, exercises or discussions in the manuals that may be triggering for clients, (ii) staff could provide optional adaptations to the delivery of traditionally therapeutic exercises that may be difficult for clients with a trauma history (e.g., mindfulness activities that focused on body awareness), (ii) in-the moment-strategies provided if clients did experience distress in the sessions (e.g., distress tolerance exercises), in addition to preventative strategies to reduce the likelihood of distress arising, and (iii) clear boundaries and expectations stated at the start of each session.

Additionally, all group sessions across the three interventions were evaluated to ensure consistent language is used and attuned to clients’ varying levels of literacy. Consistent and accessible language for clients to understand and consolidate learnings from the groups is important for empowerment, a critical component of TIC. In addition to consistency in language, a strengths-focused approach was implemented across the program, where clients’ strengths are emphasized and strength spotting in oneself and others is woven throughout the therapeutic program and other activities. This included the addition of one formalized strength-spotting group session a week where clients were encouraged to identify and provide strengths feedback to each other.

To ensure TIC practices are consistently applied across the different therapeutic interventions, a section on trauma-informed practices was added to the Grit, Healthy Recovery, and ReFrame manuals. This was designed to reinforce the strategies of creating a safe group environment, providing consistent language for concepts discussed with clients, and reinforcing the skills discussed in staff training and in the revised policies, procedures, and guidelines (outlined in The service environment section).

#### Trauma screening and feedback

Routine screening for trauma was conducted at service entry using the Primary Care PTSD Screen for DSM-5 (PC-PTSD) (64) as part of the routine measures collected by the service. Routine measures are collected using an online survey that is sent to participants once a client is entered into client-relationship management system by staff. The five-item PTSD-PC screens for PTSD symptoms over the last month, among individual who have experienced a traumatic event in their lifetime. Staff will discuss Primary Care PTSD Screen scores with clients in their first one-on-one case management session, typically occurring in the first week at the service, so that clients are provided timely and appropriate feedback on their symptoms. As outlined in Workforce development section, staff will receive training in understanding and delivering feedback on PTSD symptoms and will have ongoing supervision in this area.

#### Trauma-informed therapy

Clients with a positive screen on the PC-PTSD are assessed for symptoms of PTSD on the PCL-5 (65) with those with elevated symptoms (a score of 27+) then considered for eligibility to receive Cognitive Processing Therapy (CPT). Exclusions for the CPT component are: (a) non-fluent in English, (b) acutely suicidal, (c) a current diagnosis of schizophrenia, (d) currently experiencing a manic episode, (e) an intellectual disability that does not allow for the comprehension of the CPT material, and (f) experienced an index early childhood trauma that occurred before the age of three. Eligible clients will be offered 10 × 90 min sessions of CPT (66) delivered in-person or via telehealth/videoconference while they are in residential treatment. Clients who are discharged from the service will be offered CPT via telehealth if they have completed at least 2 sessions. The 10 sessions of CPT will be delivered twice a week over 5 weeks, to fit with the 6-week residential program [Table 2; (44)].

**Table 2 tab2:** An overview of the 10-session CPT content.

Week	Session	Content overview
Week 1	N/A	Routine screening and consenting
Week 2	Session 1	Introduction to CPT, psychoeducation, CPT overview
	Session 2	Introducing thoughts, feelings, and identifying stuck points
Week 3	Session 3	Processing events, thoughts, and feelings
	Session 4	Level of responsibility and introducing challenging questions
Week 4	Session 5	Processing challenging questions and introducing patterns of problematic thinking
	Session 6	Processing patterns of problematic thinking and introducing challenging beliefs
Week 5	Session 7	Reviewing challenging beliefs, introducing safety and trust issues
	Session 8	Processing safety and trust issues and introducing power and control issues, and esteem issues
Week 6	Session 9	Processing power and control issues and esteem issues, introducing intimacy issues
	Session 10	Processing intimacy issues, identifying future care pathways, and identifying unprocessed stuck points

Sessions were approximately 90 min long to ensure coverage of content and were scheduled with at least 3 days apart, to allow for practice between sessions. Each session was accompanied with home practice tasks where clients are asked to complete activities that map onto the concepts taught from the corresponding therapy sessions. The PCL-5 was collected at the beginning of every session to monitor symptom changes.

## Procedure

The TIC model was developed over a 6-month period during 2020, and the initial implementation, including workforce training, occurred post development of the program. All clients will receive the residential TIC model as part of routine care. The evaluation phase of the TIC model will occur over a 12-month period once the initial implementation has been completed. Client outcomes will be assessed at baseline and 1-, 3-, 6- and 12-months follow up (till December 2022). Within 1 week of entry to the service, clients will receive verbal and written information of the trial by a research assistant and informed consent will be obtained. Only the data of clients who consent to participate in the project will be used to evaluate the effectiveness of the new model. All client participants will be followed up for intent-to-treat purposes, regardless of treatment completion. Reminders to complete the survey will be sent to participants via SMS and email. At 1-month and 3-month timepoints, the online survey and reminders will be sent as part of the service’s usual Outcome Measures procedure. At 6- and 12-months, research assistants will send out the surveys (as these time-points are not part of the services usual outcome measure procedures). Participants will be followed-up over the phone by research assistants not involved in treatment delivery or model design, if the survey is not completed within 1 week. Participants will be reimbursed $20 for completing each survey.

Staff outcomes will be collected at the TIC training, and again at 3-, 6-, 12- and 18-months post-training, via online surveys sent by email from research assistants not involved in treatment delivery or TIC model design. Staff will be sent reminders to complete the surveys by these research assistants and general reminders regarding the study by their team leader. Staff who are no longer working at the service will not be followed up.

The sustainability of the TIC model will be assessed for a 12-month period after the evaluation phase is complete, to determine if delivery of the TIC model is sustained once the formal evaluation ends. All clients who enter the service consent to their deidentified data being used for service evaluation purposes. During this time, the researchers will have minimal involvement in the running of the model. Service outcomes will be collected during this period (see below for outcomes).

### Sample size calculation

A power calculation for a single-arm, repeated measure design over four time-points indicate we will require 60 clients for adequate power (0.9) to detect a moderate effect (*f* = 0.25) for primary client outcomes (estimating an error < 0.01 to correct for multiple outcomes). Given our recruitment period of 12-months, we expect an actual sample size of approximately 177 clients, and a retention rate of 81% (*n* = 143) at 1-month, 74% (*n* = 130) at 3-months, 64% (*n* = 113) at 6- and 12-months. This estimate was calculated by the recruitment rate for a similar therapeutic study held at the same facility (62). The staff sample size is determined by the number of staff at the participating facility, approximately 20 people.

### Outcomes

#### Client outcomes

Client outcomes will be collected upon entry to the residential treatment service (baseline), and again at 1-, 3-, 6-, and 12-months later. See Table 3 for the list of measures, including measures that are collected as part of routine care and the additional measures completed for the evaluation. The primary outcome for the evaluation will be substance-related outcomes, assessed via the World Health Organization Alcohol, Smoking and Substance Involvement Screening Test (ASSIST) (67) and the Australian Treatment Outcomes Profile (ATOP) (68). Quality of life is assessed by the relevant items on the ATOP. PTSD upon treatment entry is measured using the Primary Care PTSD Screen for DSM-5 (64), a brief five-item measure of symptoms of PTSD over the last month. Those with a positive screen on the PC-PTSD (scored 3+), will be asked to complete the PTSD Checklist (PCL-5) (69), a 20-item measure of PTSD symptom severity, which will be the primary outcome for the CPT analyses. Secondary outcomes include measures of depression and anxiety using the Patient Health Questionnaire (PHQ-9) (70), (9-items) and the Generalized Anxiety Disorder Scale (GADS-7) (71) (7-items), respectively. Client satisfaction will be assessed via the five-item Patient Experience Questionnaire from the Improving Access to Psychological Therapies program (72). Open ended responses will also be included to collect feedback from the participants about their level of satisfaction with their treatment and to better inform treatment procedures.

**Table 3 tab3:** Study timelines and outcomes.

	Enrolment		Treatment		Follow up			
TIMEPOINT	*-t_1_*	*-t_2_*	*t1*	*t2*	6 weeks	3 months	6 months	12 months
*ENROLMENT:*								
*Staff informed consent*	X							
*Client informed consent*		X						
*Client eligibility*		X						
*INTERVENTIONS:*								
*Model development*	X							
*Staff training*		X						
*TIC trial*								
*Sustainability*					X	X	X	X
*Evaluation:*								
*Client measures*		X			X	X	X	X
Demographics		X						
WHO-assist		X				X	X	X
ATOP		X			X	X	X	X
PHQ-9^a^		X			X	X	X	X
GAD-7		X			X	X	X	X
PTSD screen*		X			X	X	X	X
PCL-5*		X			X	X	X	X
Distress tolerance scale		X			X	X	X	X
Resilience evaluation scale		X			X	X	X	X
PEQ					X	X	X	X
*Staff measures*	X				X	X	X	X

^a^PHQ-9 includes an item on suicide ideation. If suicide ideation is endorsed daily on this item, risk management processes are followed. *Clients complete only if they report experiencing a traumatic event in their lifetime. WHO-ASSIST, World Health Organization Alcohol, Smoking and Substance Involvement Screening Test; ATOP, Australian Treatment Outcome Profile; GAD-7, Generalized Anxiety Disorder; PHQ-9, Patient Health Questionnaire; PTSD, Post Traumatic Stress Disorder Screen, PCL, PTSD Checklist; PEQ, Patient Experiences Questionnaire.

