## Ethics, adverse events, and risk management processes

The study has received Human research ethics approvals by the University of Queensland (Approval number: 2020000949) and has been approved by the treatment service and the broader service organization. All participants will have substance use problems, with likely SUDs and other mental health comorbidities. Increased vulnerability and decreased social engagement must be considered, however the project has been specifically designed to support complex and typically underserved populations. As the project will be held within a residential setting, clients will have 24-h access to support, and are connected with a community worker upon leaving the program. Any safety or urgent treatment issues will be managed as per usual safety and risk management procedures of the residential treatment facility. These processes include assessing for suicide and self-harm risk on entry, development of risk management/safety plan with caseworker, and ongoing monitoring of risk. If clients do present at imminent risk of harm or other adverse events, caseworkers will work with the clients, utilizing the client’s personalized risk management plans, including hospitalization if required. Clients learn distress tolerance skills for managing difficult emotions as part of this as part of the 6-week TIC program. Further, all therapists will be trained clinicians, experienced in managing risk, distress, and discomfort in clients.

Client’s suicide risk will be assessed at follow-ups via the Outcome Measures. If participants report suicide ideation in the past 2 weeks at 1- or 3-month timepoints, the LLW case-manager for the client will instantly be informed through a client-management system, will conduct a risk assessment, and provide the client with counseling and community support services as required. For clients who are no longer active with Lives Lived Well, the risk assessment and subsequent required supports (such as connecting to community services) will be conducted by a psychologist from the research team.

Staff will be able to report adverse effects and subsequently provided with support via weekly supervision and as needed by their team leader.

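### Two different suicidal-ideation triggers are printed, and only the less sensitive one (daily endorsement) reaches the 6- and 12-month surveys

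*Protocol article*

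**What the plan says.** Two places in the protocol article state when a survey answer about suicidal ideation leads to action.

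- **Table 3 footnote (Outcomes, Client outcomes).** The footnote belongs to the PHQ-9 row and reads: "If suicide ideation is endorsed daily on this item, risk management processes are followed". It has no time limit. Table 3 marks the PHQ-9 at enrolment and at all four follow-ups (the first is labelled 6 weeks in the table and 1 month in the text).
- **Ethics, adverse events, and risk management processes.** This section first says in general terms that "suicide risk will be assessed at follow-ups via the Outcome Measures". It then gives a specific rule: "If participants report suicide ideation in the past 2 weeks at 1- or 3-month timepoints", the case-manager is alerted at once through the client-management system, carries out a risk assessment and arranges support. The next sentence covers clients no longer active with the service, for whom the assessment and supports "will be conducted by a psychologist from the research team".

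The Procedure section explains how the surveys are run. Those at 1 and 3 months go out through the service's routine outcome system. For the later ones, "At 6- and 12-months, research assistants will send out the surveys", with the reason given in parentheses: "as these time-points are not part of the services usual outcome measure procedures".

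**The concern.** The two rules set different thresholds for the same kind of answer. One requires daily endorsement. The other requires only a report within the recall window. They also cover different visits: the daily rule follows the PHQ-9 everywhere, while the more sensitive rule names two follow-ups.

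Two consequences follow. At 1 and 3 months, staff cannot tell from the document which threshold governs. At 6 and 12 months, the daily threshold is the only stated survey trigger, so ideation present on several days but not every day calls for no stated response.

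The timing makes this worse. "The service currently provides a live-in six-week treatment program", so clients who have not been readmitted answer the later surveys after round-the-clock support has ended. The weaker trigger applies when support is thinner, in a population the article itself describes as vulnerable.

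**Working it through.** The article has no figure to reproduce here. The check sets each rule against each PHQ-9 visit.

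**Inputs**

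- Follow-up visits, from the Client outcomes section: "Client outcomes will be collected upon entry to the residential treatment service (baseline), and again at 1-, 3-, 6-, and 12-months later".
- Rule A, from the Table 3 footnote: daily endorsement, wherever the PHQ-9 is given.
- Rule B, from the ethics and risk management section: ideation reported in the past 2 weeks, no frequency stated, at 1 and 3 months.
- Entry assessment: the same section has suicide and self-harm risk assessed on entry, separately from the survey.
- Expected respondents, from the Sample size calculation section: 143 at 1 month, 130 at 3 months, 113 at 6 months and 113 at 12 months.

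**Step 1: rule by visit**

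| Visit | Rule A (daily) | Rule B (any report, past 2 weeks) | Stated response to less-than-daily ideation |
|---|---|---|---|
| Entry | applies | not stated | covered by the separate entry assessment |
| 1 month | applies | applies | risk assessment under B, none under A |
| 3 months | applies | applies | risk assessment under B, none under A |
| 6 months | applies | not stated | none |
| 12 months | applies | not stated | none |

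Rule B is stated for 2 of the 4 follow-ups and rule A for all 4. Daily endorsement is therefore covered throughout. Entry is not at issue.

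**Step 2: could other text fill the 6- and 12-month cells?**

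- The sentence about clients no longer active with the service says who does the assessment. It sets no threshold and no visit of its own, and the assessment it mentions is the one introduced in the preceding sentence, which is limited to 1 and 3 months.
- The general provisions (usual facility risk procedures, action at imminent risk, recording of spontaneous adverse-effect reports) set no threshold for a survey answer.

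Neither supplies a trigger for less-than-daily ideation at 6 or 12 months.

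**Step 3: how many answers could be affected**

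The article gives no ideation rates, so any count needs an assumption.

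- Expected forms at 6 and 12 months: 113 + 113 = 226.
- Expected forms at 1 and 3 months, where rule B acts on the same answer: 143 + 130 = 273.
- Affected forms = 226 × assumed share reporting less-than-daily ideation:
  - 2%: 226 × 0.02 = 4.5
  - 5%: 226 × 0.05 = 11.3
  - 10%: 226 × 0.10 = 22.6
  - 15%: 226 × 0.15 = 33.9

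That is about 5 to 34 forms. These are forms, not people, because one client can contribute at both visits.

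**The case against.** The strongest reply is that the two texts can be reconciled, since neither says its condition is the only one.

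- **Tiers.** Any report may lead to an assessment and daily endorsement to further processes. This is possible, but neither place says so. It would also leave less-than-daily ideation without a trigger at 6 and 12 months.
- **Footnote as definition.** The two weeks may be only the recall window, with the footnote supplying the frequency. The threshold would then be daily at every visit, and the difference between early and late follow-ups would disappear. But less-than-daily ideation would then have no survey trigger at any follow-up, which widens the gap. It is also the less natural reading. Still, it means the early-versus-late contrast depends on taking the ethics section's silence on frequency to mean any frequency.
- **The psychologist as the later route.** The sentence on inactive clients may have been meant for the later surveys. That is plausible, and it shows that a responder exists. The text does not say so, and the disagreement over threshold would remain.
- **A condensed article.** How an alert travels from a survey run by research assistants to a clinician is operational detail that an article may leave to the full protocol. This stands, so the missing alert route is not counted as an error here. It does not excuse two printed thresholds that disagree, or a printed visit limit.

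Two further points stand. The 2% to 15% range has no basis in the documents and serves only as a scale. And which threshold is right is a clinical decision that the documents do not settle.

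**Conclusion.** The concern holds. The article prints two thresholds for the same safety response, and the more sensitive one is limited to 2 of 4 follow-ups. As written, no survey trigger is stated for less-than-daily ideation at 6 and 12 months. None of the reconciling readings closes that gap.

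The mismatch in wording and visits is certain, because it is on the page. The number of answers affected is unknown; about 5 to 34 of 226 expected forms is an illustration that rests on the assumed share, and the conclusion does not depend on it. Estimates, power and inference are unaffected. It should be fixed because it concerns participant safety after clients leave residential care.

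**What to change.** Use one trigger, word it the same way in both places, and apply it at every PHQ-9 follow-up.

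1. Have the clinical leads confirm the threshold. The sensible default is the one in the ethics and risk management section: ideation reported in the past 2 weeks, at any frequency.
2. In that section, replace the restriction to two visits with *at any follow-up (1, 3, 6 or 12 months)*.
3. In the Table 3 footnote, replace the daily condition with the same trigger. If two tiers are intended, state both and what each leads to.
4. It would also help to say that 6- and 12-month alerts go to the case-manager for clients active with the service, and otherwise to the research-team psychologist already named.

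The cost is a wording change in two places and an alert setting on the 6- and 12-month surveys. The downside is some extra risk assessments, mainly for the psychologist: at most one for each affected form counted above, on the same assumption.
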